# **METHODS**

- 1. **Proposed study**

We aim to explore the effectiveness of a tailored comprehensive cardiac rehabilitation programme (both before and after the planned AF ablation) comprising of an exercise programme and patient education programme incorporating lifestyle behaviour change (CREED AF intervention). The education programme will centre on risk factor analysis with individualised risk factor targeting. This will include weight reduction support, advice on alcohol consumption and smoking cessation support. There will be risk factor modification to optimise hypertension/diabetes control, assess for presence of obstructive sleep apnoea with onward referral if needed, and advice on regular exercise. The education sessions will integrate a psychosocial well-being component to support self-management.

- 1. **Study population**

Patients with AF who are referred for first-time AF ablation at University Hospitals Coventry & Warwickshire NHS Trust.

- 1. **Intervention**

The CREED AF intervention will involve a cardiac pre/rehabilitation exercise training programme combined with a patient education programme.

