2. They will have the procedure explained to them in full detail and any questions they have will be answered.
3. A spirometry measurement of forced vital capacity will be obtained before the CPET begins.
4. A 12-lead ECG will be attached to the participant.
5. A Hans Rudolph face mask will be fitted to the participant and baseline data collected.
6. A blood pressure cuff and pulse oximeter will be attached with measurements taken at baseline and during the test.
7. The exercise protocol will begin with increasing exercise intensity until the participant feels they cannot continue, when cadence falls by 5% or more or when the individual leading the exercise test requests it to be stopped.
8. Recovery period involving low intensity exercise.
   1. **Standard Care Group**

Participants who are randomised into the control group will complete the outcome assessments at baseline and 10 weeks (±2 weeks) post-ablation. Further HRQoL questionnaires and medical records will be reviewed at 12 months (±4 weeks) post-ablation. They will also receive a 30-minute 1-to-1 education session (remotely or in person) from a CREED AF practitioner before their AF ablation to go through the risk factors of AF and what they can do to improve their health. The session will involve a discussion with the participant around risk factors related to AF and recommendations for what actions the participant should take to minimise these factors, sign-posting to publicly available patient information leaflets (e.g. <https://heartrhythmalliance.org/aa/uk/resources/arrhythmia-alliance-patient-resources>). For the rest of the trial, they will follow the standard care pathway for ablation patients.

- 1. **Intervention Group**

The CREED AF intervention will involve 2 distinct intervention strategies that come together. These strategies are the exercise intervention and the education intervention. Participants who are randomised to this intervention will have an additional consultation with a member of the research team who will go over again in more detail what the CREED AF intervention is, and what it involves for the participant.

Exercise Sessions

*Format*: To ensure generalisability to the NHS, the underpinning framework of the CREED AF exercise intervention is based on UK cardiopulmonary rehabilitation guidelines and service delivery models (62).

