All the scoring of HRQoL (EQ-5D-5L, SF-36 and AFEQT) will be computed as per the instrument algorithm. The scores will then be summarised descriptively overall and by treatment arms at baseline and the short- and long-term follow-up time points. The change of HRQoL from baseline to 10-week, from baseline to 12-month post-ablation, and the difference between treatment arms will be estimated with their associated 95% confidence intervals (CIs). We may explore the longitudinal effect of long-term HRQoL (12-month post-ablation). Proportion of significant AF event by treatment arms will be estimated with associated 95% CI using Kaplan-Meier. Similarly, the proportion of individual and composite MACE and its associated 95% CI by treatment arms will be estimated. The recurrence of AF burden from the Holter and each of the MACE occurrence will also be estimated by treatment arms as a time-to-event estimand. We will also perform a subgroup analysis by types of AF (persistent and paroxysmal AF) for all endpoints. We may also explore for any potential confounders in VO_2peak_ within the study, and the complier averaged causal effect (CACE) analysis as a sensitivity analysis.

- 1. **Procedure(s) to account for missing or spurious data**

We will endeavour to collect all data possible from each participant during their enrolment in the study. Data monitoring will be carried out by the trial manager/researcher and any missing data points will be raised as a query on the online database which will be followed up by the delivery team. If it is judged that the same critical data points (as outlined in the data management plan) are consistently being missed (>10%) then this will be raised at the following TMG for corrective action.

Multiple imputation methods will be used as secondary analysis if more than 10% of the outcome variable is missing.

- 1. **Economic Evaluation**

To assess the costs, benefits, and overall cost-effectiveness of the intervention, we will integrate a prospective economic evaluation into the trial. The time horizon of the analysis will be one year, congruently with the duration of the trial. The primary perspective will be NHS and Personal Social Services (PSS), with secondary analyses including additional patient costs accruing over the 12 months period post ablation.

Resource use and costs

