Intervention resource use and costs associated with implementing and delivering the intervention will be captured within the trial. For example, for both arms we will record and then cost the AF cryoballoon and radiofrequency ablation procedure using published costing resources such as the NICE reference costs (40,41). For the intervention arm we will additionally record and cost the resource use associated with attendance to the pre- and post-AF ablation rehabilitation intervention components. Further use of other NHS care (e.g. primary care appointments, outpatient visits, inpatient admissions) and related costs incurred by the patient (e.g. out-of-pocket expenses and time-related costs) will be captured using a resource use measure (RUM) at different points in time. To cost the intervention and healthcare resource use, we will apply unit costs using national reference sources, e.g., PSSRU (65). This will allow the calculation of total healthcare costs related to AF from baseline to 12 months for both arms of the trial including those attributable to the intervention.

Outcomes

Responses to EQ-5D-5L, a widely used preference-based quality of life instrument, collected at baseline and follow-up visits will be used to calculate quality-adjusted life years (QALYs) using UK value set recommended by NICE at the time of the analysis. Similarly, responses to the SF-36 questionnaire will be used to derive preference-based quality of life indices through the SF-6D algorithm (66). Baseline utility scores will be used both in the construction of QALYs and as an adjusting covariate within the regression analysis. Mechanisms of missingness of data will be explored, and multiple imputation will be used if missing data is prevalent.

Analysis

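### Section 10.7 is inconsistent on cost scope: it captures general NHS care but states an AF-related total with no attribution rule, while the ICER uses generic QALYs

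*Protocol*

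**What the plan says.** Section 10.7 of the Protocol opens with the viewpoint of the analysis: "The primary perspective will be NHS and Personal Social Services (PSS"), with patient costs added in secondary analyses.

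Under Resource use and costs, delivery is introduced by illustration: "For example, for both arms we will record and then cost the AF cryoballoon and radiofrequency ablation procedure". Then: "For the intervention arm we will additionally record and cost the resource use associated with attendance" at the pre- and post-ablation rehabilitation components. Beyond delivery, a resource-use measure is to pick up "Further use of other NHS care (e.g. primary care appointments, outpatient visits, inpatient admissions"), with no restriction by condition. The subsection closes on the only cost total the document states: "This will allow the calculation of total healthcare costs related to AF from baseline to 12 months for both arms of the trial". That sentence goes on to bring in costs due to the intervention.

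Under Outcomes, the QALYs are generic: "Responses to EQ-5D-5L, a widely used preference-based quality of life instrument", supplies the utilities, and SF-6D indices are derived as well. Under Analysis, the ICER is the cost difference set against the QALY difference.

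On content, section 4.1 says that the programme will "assess for presence of obstructive sleep apnoea with onward referral if needed". Section 4.3 adds alcohol, blood pressure, smoking, diabetes and weight. For the control arm, section 9.10 (Standard Care Group) says: "They will also receive a 30-minute 1-to-1 education session (remotely or in person) from a CREED AF practitioner".

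**The concern.** An ICER is interpretable when its cost side and its effect side cover the same consequences of treatment. EQ-5D-5L and SF-6D register any change in health, whatever its source. Part of this intervention is meant to work through conditions other than the arrhythmia. It may generate contacts (a sleep-clinic referral, a diabetes review, a change in blood-pressure treatment) and it may avert others. If those contacts are sorted out of the total because they are not labelled AF, their health consequences stay in the QALYs while their costs and savings leave the numerator.

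The sorting is itself a difficulty. Without a written rule, someone must decide contact by contact what is AF-related. Section 9.7 says that several team members cannot be blinded and names only the follow-up exercise-test physiologists as blinded. It does not say whether whoever does the costing would know the allocation.

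Cost-effectiveness is a named secondary objective, so this bears on a result that will be reported. The primary endpoint, peak VO2, is not touched.

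**Working it through.** The Protocol gives no cost, QALY or ICER figure, so there is no stated number to reproduce. The check is a comparison of the text plus simple arithmetic.

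**1. Scope, statement by statement (section 10.7)**
- Perspective: NHS and PSS. No limit by condition.
- Resource-use capture: other NHS care in general. No limit by condition.
- Stated total: AF-related, plus costs due to the intervention. Limited by condition, with no rule for applying the limit.
- Analysis paragraph: mean cost per patient and difference in cost. No limit by condition.
- Effects: generic utilities. No limit by condition.

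One statement of the five is narrower than the others, and it is the one that defines the total.

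**2. What the intervention clause does.** It has two readings.
- It means delivery costs only. A referral to a sleep service that is not classed as AF then falls outside the total.
- It means every cost the intervention causes. Non-AF costs then enter for one arm only, with no matching rule for the control arm or for contacts avoided.

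Neither reading gives a like-for-like comparison of arms.

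**3. Sensitivity of the ICER.** Let D be the net between-arm difference, per participant, in costs left out of the total, and let ΔQ be the QALY gain. The ICER then shifts by D/ΔQ. ΔQ is not in the Protocol; I assume 0.01 to 0.03. With D = £100:
- ΔQ = 0.03: 100/0.03 = £3,333 per QALY
- ΔQ = 0.02: 100/0.02 = £5,000 per QALY
- ΔQ = 0.01: 100/0.01 = £10,000 per QALY

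Only a difference between arms matters. If £100 per participant is left out equally in both arms, D = 0 and the ICER does not move.

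**4. Weight of the control-arm session.** Scheduled contact time, from the Study Summary and section 4.3:
- Exercise, lower end: 2 per week × 6 weeks × 2 phases × 1 h = 24 h
- Exercise, upper end: 3 per week × 8 weeks × 2 phases × 1 h = 48 h
- Intervention education: 6 × 0.5 h = 3 h
- Intervention total: 27 to 51 h
- Control session: 0.5 h, so 0.5/51 = 1.0% to 0.5/27 = 1.9% of intervention contact hours

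Hours are not costs. Group exercise is cheaper per participant-hour than one-to-one time, so the cost share may be somewhat higher, but it remains small.

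**The case against.** The strongest reply is that the AF limit rests on one phrase and that everything around it points to a full NHS and PSS costing. The perspective, the data capture and the analysis paragraph carry no such limit, and no exclusion step is described. Sections 2 to 4 also treat hypertension, diabetes, smoking, weight and sleep apnoea as AF risk factors, so their care might itself be counted as AF-related. This stands to the extent that the document does not settle that partial costs will be used. It does not dispose of the point: the phrase is the only definition of the total, and doubt over whether a sleep or diabetes contact counts is what an attribution rule would resolve. Nor is this a detail merely left to an analysis plan, since a scope is stated.

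Three stronger inferences should be resisted.

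- A reader might infer that the total contradicts the NHS and PSS perspective outright. A perspective says whose costs count, not for which conditions. The two sit badly together but are not formally incompatible.
- A reader might infer a bias in favour of the intervention. Excluded referral costs would flatter it, but excluded savings would count against it. The text gives no net sign and no evidence of a between-arm difference.
- A reader might infer that the control arm's session is left out of the costing. The list of delivery items is introduced as an example and nothing excludes the session; it is simply not named. At about 1% to 2% of scheduled contact hours it would matter little either way.

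The analysis paragraph also promises sensitivity analyses on different assumptions. That helps, but it does not say which scope is the base case.

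**Conclusion.** Section 10.7 is inconsistent about which costs enter the ICER, and its one explicit definition is narrower than both the data it collects and the outcome it divides by. Followed literally, it could leave out between-arm differences in non-AF NHS and PSS costs while counting the health effects that go with them.

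Size and direction cannot be determined from the document. The range of £3,333 to £10,000 per QALY for each £100 of net between-arm difference is an illustration resting on assumed gains of 0.03 to 0.01; it is not an estimate of the error. The control-session point is one of completeness only.

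This should be settled before the economic data are analysed. It affects a secondary objective and leaves the primary analysis unchanged.

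**What to change.** In section 10.7, define the base-case total as all NHS and PSS costs recorded in both arms over the analysis horizon, plus the delivery costs of the sessions given in each arm: the CREED AF exercise and education sessions, and the control arm's single education session. Report AF-related cost as a sensitivity analysis with a written rule, applied identically in both arms, for what counts as AF-related.

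The cost is mostly wording. The resource-use measure is already described as covering NHS care in general, and section 13 collects hospital admissions for reasons other than the ablation. The sponsor should confirm that the measure includes personal social services items, since the examples given are all NHS contacts. The statistical price is that all-cause costs vary more than AF-related costs. With 53 per arm the interval for incremental cost, and the spread on the cost-effectiveness plane, will be wider. The AF-related sensitivity analysis shows how much of that spread comes from other care.

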# **DATA MANAGEMENT**

- 1. **Data Collection and Management**

Trial data will be collected on CRFs and validated questionnaires, either on paper or electronically. An online validated, GCP compliant, Electronic Data Capture system will be used to record and store trial data. Individual user log-in access to this database will be granted to only those in the study team that require it for the performance of their role.

Screening and recruitment logs of all patients approached to take part, and participants enrolled in the trial will be held at each site. Upon confirmation of eligibility, participants will be assigned a unique trial ID, which will be used to identify all documents associated with that participant for the duration of the trial.

Participants will be also able to complete the outcome questionnaires by post or online if they prefer. If done online, they will be emailed a secure, unique link to complete the questionnaires, where their answers will directly input onto the database.

Following all query resolution, the database will be exported for statistical analysis. These procedures along with data entry instructions will be detailed in a Data Management Plan (DMP) produced by the trial manager and co-investigators.

- 1. **Access to Data**

Personal data collected during the trial will be handled and stored in accordance with the GDPR. Disclosure of confidential information will only be considered if there is an issue which may jeopardise the safety of the participant or another person, according to UHCW SOPs and the UK regulatory framework. There is no reason to expect this situation to occur in this trial more than any other.

All data will be pseudonymised after the collection of baseline demographics for each participant. Confidentiality will be strictly maintained, and names or addresses will not be disclosed to anyone other than the staff involved in running the trial. All electronic participant-identifiable information will be held on a secure, password-protected database accessible only to essential personnel. Paper forms with participant-identifiable information will be held in secure, locked filing cabinets within a restricted area. Participants will be identified by a unique trial ID only.

Direct access will be granted to authorised representatives from the Sponsor, host institution and the regulatory authorities to permit trial-related monitoring, audits, and inspections - in line with participant consent.

Requests for data sharing will be managed in accordance with UHCW policy on data sharing. The datasets generated during and/or analysed during the current study are/will be available upon request after publication of the main study results. The publication of a trial protocol, trial results and trial data will be in line with UHCW SOPs.

- 1. **Archiving**

Following the resolution of queries and confirmation of study close-out by the Chief Investigator, all essential documentation will be transferred to a third-party archiving service, which provides suitable fire and water-resistant facilities. Study files will be archived for a period of 10 years. Access to the study documentation will be restricted to named individuals within the study team with express permission from the Chief Investigator.

# **TRIAL OVERSIGHT**

- 1. **Role and Responsibilities of the Sponsor**

UHCW has agreed to act as sponsor for this trial and will undertake the responsibilities of sponsor as defined by the UK Policy Framework for Health and Social Care Research and ICH Good Clinical Practice. An authorised representative of the Sponsor has approved the final version of this protocol with respect to the trial design, conduct, data analysis and interpretation and plans for publication and dissemination of results. As sponsor, UHCW provides indemnity for this trial and, as such, will be responsible for claims for any negligent harm suffered by anyone as a result of participating in this trial. The indemnity is renewed on an annual basis and will continue for the duration of this trial.

- 1. **Role and Responsibilities of the Funder**

Funding for this trial is provided by Boston Scientific. The design and management of this trial are entirely independent of the funder.

- 1. **Trial Management Arrangements**
     1. **Trial Coordinator/Manager**

The Trial Coordinator/Manager will have responsibility for overseeing day to day coordination of the trial and reporting regularly to the TMG. The Trial Coordinator/Manager’s responsibilities include, but are not limited to:

- Coordinating protocol development, patient, and trial management documents
- Correspondence with study funder and tracking of progress against agreed milestones
- Setting up and maintaining the Trial Master File;
- Ensuring necessary approvals are in place before the start of the trial at each site;
- Providing training to trial personnel;
- Providing data management support; including data input, maintenance of the trial database and raising of queries
- Producing trial progress reports and coordinating TSC meetings and minutes;
- Ensuring data security and quality and ensuring data protection laws are adhered to;
- Ensuring complete records are in place for audit and monitoring purposes;
- Ensuring the trial is conducted in accordance with the ICH GCP;
- Archiving all original trial documents including the data forms in line with UHCW NHS Trust policy
  - 1. **Principal Investigators**

Site Principal Investigator responsibilities include, but are not limited to:

- Ensuring that the trial is conducted as set out in the protocol and supporting documents
- Delegating trial related responsibilities only to suitably trained and qualified personnel and ensuring that those with delegated responsibilities fully understand and agree to the duties being delegated to them;
- Ensuring that CVs and evidence of appropriate training for all Site staff are available in the Trial Site File
- Ensuring that all delegated duties are captured in the study Delegation Log
- Ensuring all Adverse Events are documented and reported promptly to the Trial Manager;
- Accountability for trial treatments at their site;
- Ensuring the trial is conducted in accordance with ICH GCP principles;
- Allowing access to source data for monitoring, audit and inspection;
- Ensuring that all source data is complete and provided to the Trial Manager at regular intervals
  - 1. **Trial Management Group (TMG)**

The Trial Management Group, consisting of the project staff and co-investigators involved in the day-to-day running of the trial, will meet regularly throughout the trial.

# **ADVERSE EVENT MANAGEMENT**

- 1. **Adverse Events**

An Adverse Event (AE) is defined as any untoward medical occurrence involving a participant, which does not necessarily have a causal relationship with the intervention or trial.

**Expected** **AEs,** related to the exercise outcome assessments or the exercise intervention, include ‘normal’ levels (for the individual) of:

- Breathlessness
- light headedness/dizziness
- muscle and joint stiffness/soreness
- tiredness/fatigue

There are a few AEs which are expected following AF ablation and occur after roughly 2-4% of all AF ablation cases. These AEs are listed below:

- Vascular injury
- Pericardial effusion/tamponade
- Stroke/Transient Ischaemic Attack
- Myocardial Infarction
- Phrenic nerve injury
- Atrioventricular block
- Pulmonary vein stenosis

Of these conditions there is a small risk (1:400) of requiring further cardiac surgery or a blood transfusion. Each AE will be assessed by the CI or a delegated clinician to assess causality to the CREED AF intervention. In the unlikely event that it is decided that one of the above post AF ablation conditions is related to the CREED AF intervention this will be reported as such in line with local Trust policy and national safety reporting guidelines.

Recording procedures will be the same for both trial groups. Expected AEs will be recorded on the CRF (AE form).

**Unexpected AEs** related to the exercise outcome assessments or the exercise intervention for both the intervention and usual care groups, will be recorded on the appropriate CRF (AE form) and returned routinely to UHCW. Unexpected AEs will be logged and reported at TMG meetings. Should multiple of the same unexpected AE occur during the trial period then this will trigger the TMG to review the study procedures to see if there are any changes that need to be implemented.

AEs in the intervention group will be determined through patient report at either their in-person intervention session, exercise outcome assessment (CPET) or via their 1-to-1 appointments with the research team (online, in person or over the phone), including a follow-up phone call the day after the outcomes assessment (VO_2peak_) appointments until resolution of the event. AEs in the standard care group will be determined via a check of their medical records, on the day of their exercise outcome session (CPET), and a follow-up phone call the day after the outcomes assessment (VO_2peak_) appointments until resolution of the event.

- 1. **Serious Adverse Events (SAEs)**

Over the study period, people may be admitted to hospital for reasons other than their AF ablation procedure. Admissions data will be collected from self-report and via medical records checks.

For CREED AF, an SAE will be an untoward medical occurrence that fulfils one or more of the following criteria:

- Results in death
- Is life-threatening
- Requires hospitalisation or prolongation of existing hospitalisation
- Results in persistent or significant disability or incapacity
- Requires medical intervention to prevent one of the above, or is otherwise considered medically significant by the investigator

All admissions to hospital are an SAE. The following SAEs are expected with CREED AF and **do not** require additional reporting for this trial, but must be recorded in the relevant section(s) of the CRF:

- Disease progression: worsening symptoms/AF attrition unrelated to the exercise intervention.
- Treatment, which was elective or pre-planned, for a pre-existing condition, not associated with any deterioration in condition.
- General care, not associated with any deterioration in condition.

**Reportable SAEs - intervention group:** SAEs related to exercise sessions (remote or group sessions within the Atrium Health Centre), or outcomes assessments (VO_2peak_) are possible. In the intervention group, any event that occurs at any time (remote or group sessions within the Atrium Health Centre,) between baseline outcomes assessment and the 10 weeks (±2 weeks) post-AF ablation, or within 24 hours of the outcome assessment appointments (VO_2peak_), will be recorded and reviewed by the chief investigator to determine if it is directly attributable to the intervention, and investigated in line with UHCW’s SOP. This will be determined by participant report at each intervention session or 1-to-1 education session and a follow-up phone call the day after the outcomes assessment (VO_2peak_) appointments until resolution of the event.

If a participant has not attended two consecutive in-person intervention appointments at the Atrium Health Centre, without informing a member of the CREED AF study team, their status will be checked on local electronic clinical records by the local CREED AF clinical rehabilitation team (with participant consent). If their status is unclear, the CREED AF clinical rehabilitation team will attempt to make contact on the phone at least three times.

**Reportable SAEs - standard care group**: any event occurring within 24 hours of each of the assessment appointments (baseline and 10 weeks (±2 weeks) post ablation) will be recorded and reviewed to determine if it is directly attributable to the trial; this will be determined via a phone call to the participant the day following their appointment.

All participants experiencing SAEs during the period up to the 12-month assessments or during the 24-hour periods after the baseline and 10 weeks (±2 weeks) post-AF ablation outcomes assessment (VO_2peak_) will be followed-up until resolution of the event.

The causality of SAEs (i.e. relationship to trial intervention) will be assessed by the investigator(s) using the SAE form (Table 2).

*Table 2: SAE Causal relationship*

| **Relationship**  **to trial intervention** | **Description** |
| --- | --- |
| Unrelated | There is no evidence of any causal relationship |
| Unlikely to be related | There is little evidence to suggest there is a causal relationship (e.g. the event did not occur within a reasonable time after administration of the trial intervention). There is another reasonable explanation for the event (e.g. the patient’s clinical condition, other concomitant treatment). |
| Possible relationship | There is some evidence to suggest a causal relationship (e.g. because the event occurs within a reasonable time after administration of the trial intervention). However, the influence of other factors may have contributed to the event (e.g. the patient’s clinical condition, other concomitant treatments). |
| Probable relationship | There is evidence to suggest a causal relationship and the influence of other factors is unlikely. |
| Definitely related | There is clear evidence to suggest a causal relationship and other possible contributing factors can be ruled out. |

To establish causality, the following information should be collected for each SAE:

- full details in medical terms and case description
- event duration (start and end dates, if applicable)
- action taken
- outcome
- seriousness criteria
- causality (i.e. relatedness to intervention), in the opinion of the PI
- whether the event would be considered expected or unexpected

SAEs that are deemed to be unexpected and possibly, probably or definitely related to the trial interventions or outcomes assessments, will be notified to the Research Ethics Committee (REC) within 15 days. All such events will be reported to the TMG at their next meeting.

Any change of condition or other follow-up information should be communicated to the Sponsor as soon as it is available or at least within 24 hours of the information becoming available. Events will be followed until resolution or a final outcome has been reached. A member of the PI’s trial team will be instructed to closely monitor each participant who experiences a SAE, until the outcome of the SAE has been determined.

- 1. **Responsibilities**

*Chief Investigator/delegate or independent clinical reviewer:*

- Clinical oversight of the safety of patients participating in the trial, including an ongoing review of the risk / benefit.
- Using clinical judgement in assigning seriousness and causality of SAEs where it has not been possible to obtain local medical assessment.
- Using clinical judgement in assigning expectedness.
- Immediate review of all related and unexpected SAEs.
- Review of specific SAEs in accordance with the trial risk assessment and protocol as detailed in the Trial Monitoring Plan.
- Production and submission of annual reports to the relevant REC.

*Sponsor:*

- Central data collection and verification of AEs and SAEs, according to the trial protocol.
- Delegating individuals to perform SAE causality and expectedness assessments on behalf of the Sponsor.
- Reporting safety information to the CI, delegate, or independent clinical reviewer for the ongoing assessment of the risk/benefit according to the Trial Monitoring Plan.
- Expedited reporting of related and unexpected SAEs to the REC within required timelines.
- Notifying Investigators of related and unexpected SAEs that occur within the trial.

*Trial Management Group:*

- Periodically reviewing safety data.

